## Abstract

**Introduction:**

Matching treatment to specific patients is too often a matter of trial and error, while treatment efficacy should be optimised by limiting risks and costs and by incorporating patients’ preferences. Factors influencing an individual’s drug response in major depressive disorder may include a number of clinical variables (such as previous treatments, severity of illness, concomitant anxiety etc) as well demographics (for instance, age, weight, social support and family history). Our project, funded by the National Institute of Health Research, is aimed at developing and subsequently testing a precision medicine approach to the pharmacological treatment of major depressive disorder in adults, which can be used in everyday clinical settings.

**Methods and analysis:**

We will jointly synthesise data from patients with major depressive disorder, obtained from diverse datasets, including randomised trials as well as observational, real-world studies. We will summarise the highest quality and most up-to-date scientific evidence about comparative effectiveness and tolerability (adverse effects) of antidepressants for major depressive disorder, develop and externally validate prediction models to produce stratified treatment recommendations. Results from this analysis will subsequently inform a web-based platform and build a decision support tool combining the stratified recommendations with clinicians and patients’ preferences, to adapt the tool, increase its’ reliability and tailor treatment indications to the individual-patient level. We will then test whether use of the tool relative to treatment as usual in real-world clinical settings leads to enhanced treatment adherence and response, is acceptable to clinicians and patients, and is economically viable in the UK National Health Service.

**Discussion:**

This is a clinically oriented study, coordinated by an international team of experts, with important implications for patients treated in real-world setting. This project will form a test-case that, if effective, will be extended to non-pharmacological treatments (either face-to-face or internet-delivered), to other populations and disorders in psychiatry (for instance, children and adolescents, or schizophrenia and treatment-resistant depression) and to other fields of medicine.

## Introduction

Mental disorders are a major cause of the global health burden, accounting for 23% of years lived with disability.^1^ With 350 million people affected in the world, depressive disorder is considered to be the second leading cause of the global health burden.^2^ The burden for major depressive disorders is largely due to significant deficits in treatment provision.^3^ There are a number of pharmacological and non-pharmacological efficacious interventions available for major depressive disorder and the key challenge is how best to implement these treatments in clinical practice.^4^ About 80% of people identified as suffering from depressive disorder in primary care in the UK receive an antidepressant prescription in the first year of diagnosis.^5^ However, the majority of prescriptions are for less than 30 days,^5^ while an adequate trial of antidepressants is generally recommended to be 6–8 weeks before changing or stopping the medication. Too short a duration of treatment both limits the therapeutic effect^6^ and increases the risk of withdrawal symptoms because antidepressants should be tapered off over a period of 4 weeks or more.

While a number of factors contribute to suboptimal treatment durations, two of the most prominent ones are the initial side effects of the medication and their perceived marginal efficacy. These factors are exacerbated by our current inability to predict which drug(s) will cause side effects in which patients, and which drug(s) will work most effectively for which patients. Better means of tailoring treatment to individuals are urgently needed. This has been recognised by important institutions (for instance, the National Institute for Health and Care Excellence in the UK or the Royal Australian and New Zealand College of Psychiatrists in Australia), although there are no reliable ways of doing so, to the best of our knowledge.^7^ Over the last few years, however, there has been a substantial accumulation of clinical trial data as well as long-term outcomes from ‘real-world’ datasets. The wealth of this available data, together with the development of new methods in evidence synthesis, has created major opportunities to improve patient outcomes by using existing therapies more efficiently, in a more targeted manner.^8^ Recent models have been able to predict the probability of response for a specific subgroup of patients with depressive disorder or estimate the chances that an individual will have a particular side effect.^9^ By identifying and then matching individual antidepressants to individual patients, clinicians can more precisely customise treatment to patients’ needs and thus improve their outcome.^10^

Despite recent progress in this field,^11^ psychiatry continues to lag behind other specialties like cardiology, oncology, immunology and neurology. Currently, no validated system of tailoring treatment choices is available. Indeed, matching treatment to specific patients is too often a matter of trial and error, while treatment efficacy should be optimised by limiting risks and costs and by incorporating patients’ preferences.^10^ A joint analysis of individual participant data obtained from multiple clinical trials as well as real-world studies, has the potential to provide ‘personalised’ estimates of comparative effectiveness, but also to provide ‘individualised’ predictions regarding the probability of response to treatment and of experiencing side effects.^4^ Factors influencing an individual’s drug response in depressive disorder may include a number of clinical variables (such as number and types of previous treatments, severity of illness, concomitant anxiety etc) as well demographics (for instance, age, weight, social support and family history).^4^

However, the wealth and variety of all possible such factors create its own challenges and new approaches are needed. These approaches should^12^:

Be based on robust evidence.Be acceptable to patients and clinicians.Guide treatment personalisation, incorporating patients’ views and preferences and clinical judgement.^13^
Support probabilistic decision-making.^14^

Our project, funded by the National Institute of Health Research, is aimed at developing and subsequently testing a precision medicine approach to the pharmacological treatment of major depressive disorder, which can be used in everyday clinical settings. To this aim, we will jointly synthesise data from patients with depressive disorder, obtained from diverse datasets, including both randomised trials as well as observational, real-world studies. Results from this analysis will subsequently inform a web-based platform, which will allow shared decision-making at the individual-patient level during the routine consultation between clinicians and patients (see figure 1).

**Figure 1 F1:**
[figure not shown]
Overview of the project to develop and validate the personalise antidepressant treatment for unipolar depression combining individual choices, risks and big data treatment algorithm. Evidence from individual patient data from antidepressant trials in major depressive disorder, in combination with real-word (observational) data and patient and clinician preferences (phase I), will be used to develop a web-based personalised treatment algorithm (phase II). The web-based algorithm will be tested in a multicentre, pragmatic, randomised controlled trial comparing the treatment algorithm with usual care (Phase 3).

## Methods and analysis

This project is called ‘personalise antidepressant treatment for unipolar depression combining individual choices, risks and big data’ (PETRUSHKA) and its overarching objectives are to:

Summarise the highest quality and most up-to-date scientific evidence about comparative effectiveness and tolerability (adverse effects) of antidepressants for major depressive disorders in adults, develop and externally validate prediction models to produce stratified treatment recommendations.^15^
Build a decision support tool combining the stratified recommendations with clinicians and patients’ preferences, to adapt the tool, increase its reliability and tailor treatment indications to the individual-patient level.Test whether use of the tool relative to treatment as usual in real-world clinical settings leads to enhanced treatment adherence and response, is acceptable to clinicians and patients, and is economically viable.

To achieve these objectives, the project is structured in three phases: (1) development and validation of the models that predict clinical outcomes for patient subgroups and different treatments, (2) building a treatment algorithm, (3) designing and conducting a pragmatic randomised trial to evaluate the usefulness of the algorithm. Patients and clinicians will be involved throughout the project to understand preferences and values in relation to clinical outcomes; and acceptability of and trust in the decision support tool.

### ​Phase I: development of prediction models, using randomised and real-world evidence

When several treatment options are available, standard meta-analyses provide only partial information on relative treatment effects because they can only compare two treatments at a time.^16^ This fragmented approach does not support optimal clinical decision making^17^ and the need for a robust method to summarise evidence across several interventions has been increasingly recognised.^18^ Network meta-analysis (NMA) has been developed to allow the estimation of the relative effect of many treatments one against the other and produce ranked treatment options.^19^

In this project, we will use aggregate and individual-patient data (IPD) from multiple sources, combining methods from IPD network meta-regression and prognostic modelling.^20^ Our aim will be to predict the effects (in terms of efficacy, acceptability and tolerability) of different antidepressants given information on patient-level characteristics. Our models will incorporate a range of possible prognostic factors and effect modifiers. We will use information on both demographic (ie, gender, age, ethnicity, marital status, childhood trauma) as well as clinical characteristics (ie, family history, previous episodes, past treatments, age at onset, duration of index episode, severity, treatment dose, concomitant medication, comorbidity).^21^ We will explore a range of alternative modelling approaches, incorporating evidence from both randomised and observational evidence, utilising and further extending recently proposed methods.^22^ In addition, we will explore advanced machine learning techniques for prognostic modelling, such as artificial neural networks and support vector machines.^23^ We will finally choose the best performing models for each outcome using extensive cross-validation.

The randomised studies selected for the IPD analysis will follow the same selection criteria as our previously published NMA based on aggregate data.^24^ The review protocol with all the methodological details has already been published.^25^ We are aware that not all of the studies selected for inclusion will have data available at the individual patient level; however, we will systematically request access by contacting study authors and/or sponsors and by submitting applications via online platforms. To complement the randomised data and to also collect information about long-term outcomes (especially adverse events), we will use large observational datasets. Real-world routinely collected data may be more representative of the patient population seen in everyday clinical practice. These data will contribute by providing relevant information on the natural course of the condition and the prevalence of various important patient characteristics. We aim to use data from both primary care (QResearch - https://www.qresearch.org/), as well secondary care (UK Clinical Record Interactive Search).^26^

After model development, in order to externally validate all of our models we will use a part of the observational data as ‘ground truth’ test data (‘held-out data’). We will select a specific subgroup of the data, for example, data collected in a specific geographic location and use this approach to test our models, that is, to assess their predictive performance in real-world settings. Overall, our approach aims to harness the strengths of both randomised and observational data.

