### ​Phase 2: development of the treatment algorithm

We will then develop a clinical support system (*treatment algorithm*), to guide clinicians, patients and carers in the shared process of decision-making in routine care. Treatment algorithms have contributed to advances in many fields of medicine and psychiatry,^27^ and computerised decision systems have been developed to provide ongoing assistance to clinicians.^28^ However, existing algorithms in psychiatry lack the ability to apply the best knowledge directly to the individual patient and selectively provide information relevant to the characteristics and circumstances of that patient in their specific situation.

We will develop a web-based algorithm that will:

Utilise the predictions from the predictive models developed in phase I.Incorporate preferences and values of clinicians and patients to identify the desired clinical outcome,^29 30^ considering both efficacy and adverse events (for instance, some patients may want to avoid sedation while others tremor or sexual dysfunction).Generate the corresponding ranking list of personalised treatment recommendations that will inform the clinical discussion between clinicians and patients, and the final treatment decision.

The algorithm will be implemented in the form of a web application, accessible from any computer or tablet. The input of the algorithm will be a patient’s individual characteristics and preferences. The output will be the models’ estimates regarding the expected outcomes under each treatment, and a proposed treatment ranking according to the patients’ preferences.

During the development of the algorithm, we will organise a series of focus groups with patients, carers and clinicians to gather feedback about the layout of the decision tool, its clinical value, practical utility, and ways to improve it.

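### Held-out observational records test the predicted outcome on the drug received, so they do not by themselves externally validate the between-drug differences behind the ranking

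*Protocol article*

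**What the plan says.** All references are to the protocol article.

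- **Target (Phase I section).** "Our aim will be to predict the effects (in terms of efficacy, acceptability and tolerability) of different antidepressants given information on patient-level characteristics". The models are built by "incorporating evidence from both randomised and observational evidence", and the best one for each outcome is chosen by cross-validation.
- **External test (Phase I section).** After development, "in order to externally validate all of our models we will use a part of the observational data as" 'ground truth'. The test set is a part of the same observational sources: "We will select a specific subgroup of the data, for example, data collected in a specific geographic location". Its purpose is "to assess their predictive performance in real-world settings". No other external test set is named.
- **Role of the observational data (Phase I section).** "These data will contribute by providing relevant information on the natural course of the condition", together with the prevalence of patient characteristics and long-term outcomes.
- **Output (Phase 2 section).** The tool gives the expected outcome under each drug, and it will "Generate the corresponding ranking list of personalised treatment recommendations".
- **Use (Phase 3 section).** The algorithm is the randomised intervention, compared with usual care.

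The first objective, at the start of Methods and analysis, includes external validation of the models that produce the stratified recommendations.

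**The concern.** The stated test does not match the stated target. The target is a contrast: how this patient would fare on drug A compared with drug B. The test scores a single prediction per patient, for the drug that patient was given. Prescribers choose drugs partly on features that also predict discontinuation. To the extent that the record misses those features, the outcome pattern by drug mixes the drug's effect with the kind of patient who received it.

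Two errors are then possible. A model whose between-drug differences are wrong can look well calibrated, because it has learned the prescribing pattern that is also present in the test set. A model whose differences are right can look miscalibrated by drug. A geographic split does not remove this if prescribers in the held-out region choose drugs in a similar way.

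At stake is the claim that the recommendations were externally validated before the tool entered the trial. If the individual contrasts are poor, the trial tests a weaker intervention than intended.

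**Working it through.** The article gives no validation figure to reproduce, so the check has two parts.

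**1. Target and test side by side**

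| Step | Quantity concerned |
|---|---|
| Aim of the models (Phase I) | Effects of different drugs, given patient characteristics |
| Tool output (Phase 2) | Outcome under each drug, and a ranking |
| External test (Phase I) | Predictive performance in held-out observational records, i.e. outcome on the drug received |
| Model selection (Phase I) | Cross-validation; the article does not say whether contrasts are scored |

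Write x for measured characteristics, a for the drug and y for discontinuation. The ranking needs P(y | x, drug set to a) for every a. The held-out records give P(y | x, drug prescribed = a). The two are equal only if, given x, prescribing is unrelated to other causes of y.

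**2. Can the mismatch change which model looks better?**

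This was simulated. Every parameter is assumed; none comes from the article.

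- x (measured) and u (unmeasured) are independent standard normal variables.
- Prescribing: logit P(drug B) = b·u, with b = 0, 0.5 or 1.0.
- Outcome: logit P(discontinue) = −1.4 + 0.6x + 0.8u − 0.4·(drug B).
- True average risk difference, B minus A: −0.057. Drug B is better.
- Two logistic models in x, drug and their product: one fitted to 200,000 observational records, one to 400,000 randomised patients from the same population.
- Both are scored on 200,000 further observational records. O/E is observed over expected events.

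| b | Model fitted to | Predicted difference B−A | AUC | Brier | O/E drug B | O/E drug A |
|---|---|---|---|---|---|---|
| 0 | observational | −0.054 | 0.655 | 0.1560 | 0.99 | 1.01 |
| 0 | randomised | −0.054 | 0.655 | 0.1560 | 0.99 | 1.01 |
| 0.5 | observational | −0.004 | 0.645 | 0.1569 | 1.01 | 1.00 |
| 0.5 | randomised | −0.055 | 0.638 | 0.1576 | 1.14 | 0.88 |
| 1.0 | observational | +0.039 | 0.651 | 0.1550 | 1.00 | 1.01 |
| 1.0 | randomised | −0.055 | 0.629 | 0.1573 | 1.23 | 0.78 |

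The gap between −0.054 or −0.055 and the true −0.057 is sampling error.

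Reading the table:

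- With b = 0 the held-out records are informative about the contrast, and both models pass.
- With b = 0.5 the observational fit misses 0.057 − 0.004 = 0.053 of the true difference, yet scores better on AUC, Brier and calibration by drug.
- With b = 1.0 the observational fit reverses the ranking and still scores better on all three.

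The two models are extremes. The planned models combine both kinds of evidence and would lie somewhere between them.

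**The case against.** Four points on the other side have weight.

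*The models do not rest on observational data alone.* They draw on randomised evidence through individual-patient-data network meta-regression and are selected by cross-validation. A reader might infer that the ranking enters the trial wholly unvalidated, and the article does not support that. What can be said is narrower: the contrasts are not shown to be externally validated. Cross-validation is internal, and no contrast measure is stated for it. Nor does the article say that held-out performance will be used to choose between models.

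*Observational records can inform contrasts.* A reader might infer that they never can. That is too strong: the b = 0 rows show otherwise, and adjustment for measured confounders helps. Severity, past treatments and comorbidity are listed model inputs. The article does not say how completely routine records hold them, and its Discussion concedes that these data lack standardisation.

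*A condensed article leaves metrics, folds and adjustment to a fuller document.* That is fair, and those gaps are not the point. The point is the stated choice of one observational test set as 'ground truth' for all models.

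*The stated purpose is already limited to real-world predictive performance.* This is largely true of that sentence. However, the first objective ties external validation to the models behind the treatment recommendations, and no other external test is offered for them.

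A reader might also infer that the trial is biased or that a null result could not be explained. Neither follows. Randomisation against usual care tests the tool as a whole, whatever the quality of its ranking. Average comparative evidence would remain in the ranking even if individualisation failed. Study of how the tool is used and follow-up interviews are planned.

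**Conclusion.** The concern holds in a limited form. External validation as described scores outcomes on the drug received, in records where drug choice was not randomised. Good performance there does not by itself validate the predicted between-drug differences, and under unmeasured confounding it can favour a model that ranks wrongly. The contrasts are therefore not shown to be externally validated before the tool enters the trial.

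The size cannot be fixed from the documents. Under the assumed parameters it runs from no discrepancy (b = 0), through near-complete loss of a 5.7-point difference (b = 0.5), to a reversed ranking (b = 1.0). This depends on how much of what drives prescribing is missing from the records, and the article gives no figure for that. The conclusion bears on the external-validation objective and on how well supported the intervention is. It does not bear on the validity of the randomised comparison.

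**What to change.** 1. Keep the held-out observational region as the test of absolute-risk prediction in UK practice, and limit the claim from it to that. Do not call it 'ground truth' for relative effects.
2. Add leave-one-trial-out (internal-external) validation across the randomised individual-patient-data trials that are obtained. Refit the model without each trial in turn, predict that trial's drug-versus-drug differences, and compare them with the observed randomised differences. One usable summary is the observed outcome in patients randomised to the higher-ranked drug against those randomised to the lower-ranked drug.
3. Report the two results separately: real-world absolute risk, and randomised contrasts.

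The cost is extra analysis time. Precision will be limited if few multi-arm or head-to-head trials are obtained, which is a real possibility: the article expects that not all studies will have individual data and names access to such data as a main barrier. Permanently reserving whole trials would be a heavier trade-off and is not needed, because under leave-one-trial-out every trial returns to the final model fit. Trial populations are also more selected than routine patients, so this step supplements the observational test and does not replace it.

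### Testing all models on one non-random subgroup of the development records is geographic rather than external validation for models that use those records, and one location cannot show regional variation

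*Protocol article*

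**What the plan says.** The first overarching objective under Methods and analysis is to "develop and externally validate prediction models to produce stratified treatment recommendations".

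The Phase I section gives the route:

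- **Development.** A range of modelling approaches will be explored, "incorporating evidence from both randomised and observational evidence". The observational sources named are one UK primary-care and one UK secondary-care record system.
- **Selection.** "We will finally choose the best performing models for each outcome using extensive cross-validation".
- **Validation, after development.** "in order to externally validate all of our models we will use a part of the observational data". The part is described as follows: "We will select a specific subgroup of the data, for example, data collected in a specific geographic location". The stated purpose is "to assess their predictive performance in real-world settings".

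No separate data source is named for validation, and no rotation of the held-out part is mentioned.

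Two later sections show what the models are for. Under Phase 2, the tool shows users the expected outcomes under each drug as well as a preference-weighted ranking. Under Phase 3, it is used in primary and secondary care in centres across the UK, with later use in other countries in view.

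**The concern.** The question a user of the tool needs answered is how well its predicted risks hold in a place that did not contribute to the model. That is a question about the distribution of calibration and discrimination over places. A single held-out location is one draw from that distribution. It may be easy or hard to predict, and nothing in the result shows which.

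The label adds to this. A reader who sees that all models were externally validated will assume a test in an independent source. For models fitted partly or wholly to the records, the test data are a slice of the source that built them.

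At stake is what can honestly be said about the tool when it enters the trial. Because absolute expected outcomes are displayed to patients and clinicians, calibration matters as well as rank order. The records are also brought in partly to describe the natural course of the condition in everyday practice, and that background risk could plausibly differ between places.

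**Working it through.** **1. The plan's own figure.** There is none to reproduce. The article gives no number of regions, size of held-out set, performance measure or precision for this step. The check is therefore one of logic, followed by illustrations whose inputs are assumptions.

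**2. Side by side.** Development uses randomised and observational evidence. The test set is part of the observational data, and no other validation source is named. Hence:

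- for a model that uses the records, the test data come from the development source, separated by place if the geographic example is followed;
- for a model fitted to randomised data only, the records are a genuinely different source, and the word external is fair.

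The plan applies one label to both.

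**3. What one location can estimate.** Let the estimate in region r be μ + u_r + e_r, with between-region SD τ and sampling error SE. With K regions, τ has K − 1 degrees of freedom. With K = 1 this is 0, so τ cannot be estimated.

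**4. Illustration on absolute risk.** Assumptions, not in the documents: calibration-in-the-large varies between regions with logit-scale SD τ of 0.1, 0.2 or 0.3, and the predicted risk is 25%.

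*Case A: the held-out region happens to be average.* The 95% range of true risk over regions is expit(logit 0.25 ± 1.96τ), with logit 0.25 = −1.0986.

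*Case B: the held-out region is itself a random draw, and the average is otherwise unknown.* The difference between two regions has SD √2·τ, so the range is expit(logit 0.25 ± 1.96·√2·τ).

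| τ | Case A | Case B |
|---|---|---|
| 0.1 | 21.5–28.9% | about 20–31% |
| 0.2 | 18.4–33.0% | about 16–37% |
| 0.3 | 15.6–37.5% | about 13–43% |

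Case A is the narrower reading. In either case a hold-out showing 25% predicted and 25% observed looks perfect.

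**5. Illustration on discrimination.** Assumptions, not in the documents: within-region SE of the c-statistic 0.005, and τ of 0.01, 0.02 or 0.04. The naive 95% half-width from one region is 1.96 × 0.005 = 0.0098. The true SD of one region's estimate about the mean is √(τ² + SE²), so coverage of the mean performance is 2Φ(0.0098/√(τ² + SE²)) − 1. For K = 10 rotated regions, with s = √(τ² + SE²):

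- the half-width of the 95% CI for the mean is t(K−1)·s/√K;
- the half-width of the prediction interval for a new region is t(K−2)·√(τ² + s²/K).

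| τ | Coverage, one region | CI half-width, K = 10 | Prediction half-width, K = 10 |
|---|---|---|---|
| 0.01 | 62% | 0.008 | 0.024 |
| 0.02 | 37% | 0.015 | 0.049 |
| 0.04 | 19% | 0.029 | 0.097 |

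With K = 5 the prediction half-widths are 0.036, 0.070 and 0.140. The K-region intervals treat regional estimates as independent. That is approximate, because training sets overlap when regions are rotated.

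**The case against.** The case on the other side has real force on several points.

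- **Location is only an example.** This stands: the split is not fixed. The text does describe a single specific subgroup, however, and gives no hint of rotation.
- **A condensed article leaves detail to the full phase I plan.** This stands for fold structure, performance measures and set sizes, and their absence is not the point here. The point is the design and label that the article does state.
- **A geographic split is a recognised design and stricter than a random split.** This stands. The label is generous for record-based models, not plainly false.
- **A rotating hold-out can cost the safeguard of an untouched test set.** This stands if one loop is used both to pick the winner and to report its performance, because that builds in selection optimism. Nesting the selection removes the optimism, and a region can still be reserved.

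A reader might also infer stronger things that the article does not support:

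- *That only one performance figure will be reported.* There are several outcomes and two care settings. The defensible statement is one estimate per model, outcome and measure.
- *That data are wasted.* The datasets are called large, no sizes are given, and a final refit on all data is not excluded.
- *That coding is identical on both sides of the split, or that patients appear in both record systems.* Neither is stated.
- *That cross-validation folds cut across regions or studies.* The folds are not described, so region-based folds are not ruled out.

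**Conclusion.** The concern holds in a limited form. For models that use the records, the planned test is geographic validation within the development source, and a single location carries no information on between-region variation. That follows from the text and needs no assumption beyond taking the single subgroup as written.

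The size cannot be derived from the documents. Under assumed logit SDs of 0.1 to 0.3, the unseen spread around a 25% risk runs from about 22–29% to about 16–38% when the chosen region is average, and is wider when it is not.

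A reader might set that spread against the trial's 10-point target difference. The comparison is not valid. The target is a contrast between randomised arms, while the spread is in background risk. Nor does the spread by itself imply wrong recommendations: a logit shift common to all drugs leaves their order on a single outcome unchanged. What it does affect is the absolute outcomes shown to users. It could also affect trade-offs between outcomes if preferences are weighed against absolute probabilities, but the article does not give that formula.

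The phase 3 comparison, with its individual randomisation, is not affected. This is a correction to what is claimed about the tool beforehand, and is worth making before the model is fixed.

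**What to change.** 1. **Rotate the held-out region** (leave-one-region-out, that is, internal-external cross-validation). For each region, set it aside, carry out the whole model selection inside the remaining data, fit, and evaluate in the region left out. The nesting is essential, because it keeps the reported performance free of selection optimism.
2. **Report variation.** Summarise calibration-in-the-large, calibration slope and discrimination by random effects over regions, with the between-region heterogeneity and a prediction interval for a new region.
3. **Refit** the chosen model on all data for use in the tool.
4. **Optionally reserve one region**, named in advance, as an untouched final test alongside the rotation.
5. **Name it accurately.** Use geographic or internal-external validation for models that use the records. Keep the word external for models fitted only to randomised data and tested in the records.

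Cost: more computing, some rewording, and a less simple headline figure if no region is reserved. No new data are needed, and nothing in the phase 3 design changes.
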